### Recruitment and eligibility criteria

2.2

A total of *N* = 400 rehabilitants are planned to be included in the study. Participants with various indications will be recruited during inpatient psychosomatic, orthopedic, or cardiological treatment in four rehabilitation centers in Germany. Rehabilitation entails an intensive examination, information about the individual's disease or disability, and the definition of rehabilitation goals to be achieved through various on-site measures. Patients are taught coping strategies to help them cope with the illness or disability in everyday life after rehabilitation. Since the majority of patients in rehabilitation are currently unable to work or are at risk of reduced earning capacity, this also entails dealing with occupational problems. Medical rehabilitation typically lasts 3 weeks. Psychosomatic rehabilitation typically last five or six weeks.

All rehabilitants are screened for eligibility based on clinical routine data through the clinic staff of the rehabilitation centers. The inclusion criteria are: (1) planned return to work (full- or part-time); (2) age 18 to 65 years; (3) (undisturbed) access to a computer/mobile device and the internet; and (4) German Pension (federal or regional) or statutory health insurance as rehabilitation institution. The exclusion criteria are (1) current unemployment or reduced earning capacity pension with no immediate prospect of employment and (2) negative prognosis for employment (ability to work on the general labor market <3 h as assessed in rehabilitation). No specific diagnoses will be excluded from participation.

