#### Primary outcome

2.6.1

The primary outcome will be work status at six (T2) and 12 (T4) months follow-up assessment. Work status at 6 months will be considered as primary endpoint and is defined as positive if the participant is working (no unemployment, no reduced earning capacity pension) and reports a maximum of six weeks of sick leave not related to graded return to work. Work status at 12 months is defined as positive if the participant is working and reports maximum 12 weeks of sick leave not related to graded return to work. These cut-offs were chosen in line with previous analyses of return to work in German rehabilitation (Mau et al., 2002; Bethge et al., 2011). We do not include sick leave during a graded return to work measure, as participants are formally on sick leave, receiving financial support from their healthcare provider, but are back at their workplace.

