#### Secondary outcomes

2.6.2

Successful completion of a graded return to work is assessed with self-constructed items about the planning, execution, completion, discontinuation, and early termination of the measure.

Successful application for benefits for participation in working life is assessed with self-constructed items about the planning, execution, and completion of an application, as well as the (partial) approval or rejection of benefits.

Current work ability is assessed with the Work Ability Score (WAS), the first single-item question in the well-established Work Ability Index (WAI; Hasselhorn and Freude, 2007). Participants rate their current work ability compared with their lifetime best. The scale ranges from 0 to 10.

Social-medical risk index is assessed with the short and validated ‘Screening Instrument for the Assessment of Need for Occupational Related Treatment in Medical Rehabilitation’ (SIBAR; Bürger and Deck, 2009) which comprises three subscales: (1) the social-medical index (risk of early retirement); (2) occupational stress, and (3) the subjective need for occupation-related treatment. We will assess scale 1 and scale 2. The social-medical index ranges from 0 to 19. A need for occupational treatment is indicated if the score is 8 or higher. The single global rating on occupational stress of subscale 2 is: ‘Overall, my professional situation is… very stressful… to … very fulfilling’ measured on a five-point Likert scale from 0 to 4. The retest-reliability of the different subscales ranges from rep = 0.37 to rep = 0.96 in a previous study by Bürger and Deck (2009).

Subjective prognosis of gainful employment is assessed by a 3-item scale measuring the subjective prognosis of future work capacity and employment status (SPE scale; Mittag and Raspe, 2003).

Health related quality of life is assessed through the European Quality of Life Questionnaire (5 Dimensions; EQ-5D; Ludwig et al., 2018). The instrument includes a vertical EQ Visual Analogue Scale (EQ-VAS), which provides a single global rating of self-perceived health. The scale is measured on a Likert scale from 0 to 10 (0 = ‘worst imaginable health’ to 100 = ‘best imaginable health’).

Somatic symptoms are assessed with the symptom scale-8 (SSS-8; Gierk et al., 2014). The 8 item scale assess different symptoms on a Likert-scale ranging from 0 = ‘not at all‘ to 4 = ‘very much’. An example item is ‘During the past 7 days, how much have you been bothered by back pain?’.

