### Sample size

2.7

The sample size was determined a priori using SAS 9.4 software. A Power analysis based on a power of 0.80, two-sided testing, an alpha-rate of 5 %, and a randomization ratio of 3:1 was conducted. According to Bethge (2017), Odds Ratios of 3.49 (referring to Streibelt and Bethge, 2014) and 2.41 (in Bethge et al., 2011; overall in Streibelt and Bethge, 2014) were observed for work-related occupational rehabilitation programs versus medical rehabilitation with regard to work status 6 months after discharge from rehabilitation. We plan more conservative with an Odds Ratio of 2.0. According to Bethge (2011), a work status rate of 51 % in the CG could be assumed. These assumptions resulted in a total sample size of *N* = 360 required for 80 % power and a binary logistic regression model to analyze the primary endpoint. When considering a correlation of ρ = 0.4 with indicators of specific occupational problems (at least 3-months of incapacity to work before rehabilitation, unemployment at the time of application, and the socio-medical assessment of limited performance in the last occupational activity; see also Bethge, 2017), the sample size can be reduced by ρ2 = 16 % to *N* = 320, due to the reduction of total variance through the explained variance of the covariates. Based on an estimated dropout rate of 20 % at the follow-up assessments T1 (at the end of the *GSA-Online plus* intervention) and T2 (at the end of the *marena* intervention) we plan to randomize *N* = 400 patients.

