### Statistical analysis for primary and secondary outcomes

2.9

All data analyses will be performed after completion of data collection and on intention-to-treat basis. The significance level for all analyses will be defined as *p* = .05. If appropriate, results will be displayed by adjusted estimates from the analysis model, and their respective 95 % confidence intervals. Descriptive statistics will be used to describe demographics and baseline characteristics. To examine differences between IG and CG in the dichotomous primary outcome work status at 6 months (T2, primary endpoint) and 12 months (T4, secondary endpoint), a binary logistic regression model with fixed and random effects will be performed. In the logistic regression model the following parameters will be considered as fixed effects: treatment group (IG/CG), study site, operating system (android/iOS), at least 3-month incapacity for work before rehabilitation (yes/no), and unemployment at the time of admission to rehabilitation (yes/no). The social-medical risk index (SIBAR) as a continuous parameter will serve as a random effect. In addition, per protocol analyses will be performed to examine the impact of dropouts on study results. Dichotomous secondary outcomes will be analyzed accordingly. Continuous outcome measures will be analyzed with a covariance model for repeated measures. Compound symmetry will be assumed. Additionally, per protocol analyses (based on data of those participants who completed at least the lower quartile of tasks provided in *marena* in relation to the sample and participants who wrote at least the lower quartile of diary entries written in the *GSA-Online plus* sample) will be performed to examine the impact of dropouts on study results. Furthermore, other possible influencing factors (e.g., IG subgroup 1 and IG subgroup 2, received aftercare vs. not received aftercare) will be examined in an exploratory way. The results will also be displayed by rehabilitation center to explore whether obvious differences in effect sizes by rehabilitation center are apparent.

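### The primary logistic model names the continuous SIBAR score as its random effect without a grouping factor, so the text does not define one primary model

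*Protocol article*

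**What the plan says.** The article names one primary endpoint in 2.6.1: "Work status at 6 months will be considered as primary endpoint". That is one binary value per patient.

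For this endpoint, and for work status at 12 months, section 2.9 says that "a binary logistic regression model with fixed and random effects will be performed". The fixed effects are "treatment group (IG/CG), study site, operating system (android/iOS), at least 3-month incapacity for work before rehabilitation (yes/no), and unemployment at the time of admission". SIBAR is not among them. It follows in a sentence of its own: "The social-medical risk index (SIBAR) as a continuous parameter will serve as a random effect". No grouping factor, random intercept or random slope is defined. Dichotomous secondary outcomes are to be handled in the same way.

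Section 2.6.2 describes the score: "The social-medical index ranges from 0 to 19". Table 2 schedules it at all five assessments (T0 to T4), and 2.9 does not say which one enters the model. The only natural clusters are the clinics: section 2.2 recruits during psychosomatic, "orthopedic, or cardiological treatment in four rehabilitation centers in Germany". Study site is already a fixed effect.

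The sample size in 2.7 is based on a binary logistic regression and mentions no random effect.

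**The concern.** In a mixed model, an intercept or a slope varies over the levels of some unit, such as a site or a patient with repeated outcomes. A continuous baseline score is not such a unit. It is something whose coefficient may vary over units, and the text names none. The word continuous argues against treating score values as clusters, and the words random effect argue against an ordinary covariate. A programmer who follows the sentence has to choose a model that the sentence does not give.

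The affected model produces the primary odds ratio, and 2.9 extends it to the dichotomous secondary outcomes. The analyst would be left with a choice that the plan should have closed before the data are seen.

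**Working it through.** **1. The plan's own figure, and the model behind it.** Section 2.7 uses "power of 0.80, two-sided testing, an alpha-rate of 5 %, and a randomization ratio of 3:1", a control rate of 51 %, and the statement "We plan more conservative with an Odds Ratio of 2.0".

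- Intervention rate: odds 2 × 0.51/0.49 = 2.0816, so p₂ = 2.0816/3.0816 = 0.6755.
- Pooled rate at 3:1: 0.25 × 0.51 + 0.75 × 0.6755 = 0.6341.
- n(control) = [1.960·√((4/3)·0.6341·0.3659) + 0.8416·√(0.51·0.49 + 0.6755·0.3245/3)]² / (0.6755 − 0.51)² ≈ 89.8, so 90.
- Total 4 × 90 = 360, as stated.

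The 360 is thus a comparison of two proportions with no random effect. With 20 % dropout, 400 × 0.80 = 320 patients are evaluable, or 80 control and 240 intervention. The checks below use this number.

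**2. What the sentence could mean.** Let S be the SIBAR score and x the listed fixed effects.

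- Fixed covariate (not what is written): logit p = x′β + γS.
- (a) Single random coefficient: x′β + bS, with b ~ N(0, τ²). There is one draw of b in the whole trial.
- (b) Random intercept per score value: x′β + u(S), with u ~ N(0, τ²) over up to 20 unordered values.
- (c) Random slope by site with no mean slope: x′β + b(site)·S.
- (d) Patient-level slope: x′β + b(i)·S, with one binary outcome per patient.

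**3. Simulation.** Taken from the documents: N = 320, 3:1 allocation, four sites, the listed fixed effects, odds ratio 2.0 (used here as the true conditional value). Assumed: SIBAR approximately normal with mean 8 and SD 4, rounded and clipped to 0–19; log-odds slope 0.1, 0.2 or 0.3 per point. There were 200 trials per slope. Fits used the Laplace approximation, with 15-point Gauss-Hermite quadrature for (d). The factor column is the size of the difference from the fixed-covariate odds ratio in the same data, in either direction.

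| Reading | Median OR at slope 0.1 / 0.2 / 0.3 | Factor: median (95th percentile) | Power |
|---|---|---|---|
| Fixed covariate | 1.96 / 2.08 / 2.14 | reference | 0.690 / 0.720 / 0.705 |
| (a) single coefficient | 1.94 / 2.06 / 2.13 | about 1.005 (1.01–1.02) | 0.675 / 0.715 / 0.705 |
| (b) intercept per value | 1.94 / 2.05 / 2.03 | 1.03–1.06 (1.12–1.16) | 0.655 / 0.695 / 0.675 |
| (c) slope by site, no mean | 1.93 / 2.04 / 2.11 | 1.02–1.03 (1.06–1.10) | 0.645 / 0.695 / 0.700 |
| (d) patient-level slope | 4.30 / 5.57 / 8.49 | 2.0–3.7 (extreme tails) | not computed |

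Under (d) the variance ran to the imposed bound in at least 10 % of trials. One binary outcome per patient carries practically no information on it.

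The Monte Carlo standard error of each power is about √(0.7 × 0.3/200) = 0.032. The readings share the same simulated data, so their differences are less noisy than that, but small ones should not be over-read.

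**4. Power loss under (b) when SIBAR is strongly prognostic.**

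- Slope 0.3 above: 70.5 − 67.5 = 3.0 points.
- Simulation with marginal odds ratio 2.0, SIBAR-outcome correlation 0.4 (assumed) and 600 runs: 83.5 − 80.5 = 3.0 points.
- A further check with a strong SIBAR effect: 81.5 − 75.5 = 6.0 points. In that check reading (a) matched the fixed covariate (odds ratio 2.24 against 2.26, power 0.815 for both).

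Power in step 3 is lower throughout because 2.0 is there the conditional odds ratio. In the 600-run simulation 2.0 is the marginal value, and the SIBAR-adjusted mean was 2.29.

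**The case against.** The best defence is that the most literal reading does no harm. A continuous score as a random effect most naturally means one random coefficient on the score, and numerically that is a lightly shrunken covariate. In a separate run of 300 trials at a correlation of about 0.35, reading (a) gave power 0.80 and odds ratio 2.26, against 0.80 and 2.27 for the fixed covariate, and no trial changed its significance verdict. This stands, and it limits the size of the point. It does not make the sentence a definition, because nothing in 2.9 selects (a) over (b), (c) or (d).

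It could also be said that a random SIBAR slope by site is a legitimate model. It is, alongside a fixed SIBAR slope, but 2.9 states neither part. Nor is this a detail left to an analysis plan: the article makes a positive statement, which a sound analysis plan would have to contradict.

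Some stronger conclusions are tempting, and the documents do not support them.

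- **SIBAR could drop out of the model at a cost of about 8 points of power** (83.5 % with it, 75.2 % without, at correlation 0.4). That would need the variance component to collapse to zero while the score is strongly prognostic. At a correlation of about 0.35 it collapsed in 0 of 300 trials under (a) and (b). At about 0.09 it collapsed in 26 % and 53 % of runs, but there omitting SIBAR costs nothing (power 0.74 against 0.74).
- **Odds ratios of 2.00 without SIBAR and 2.29 with it show instability.** That gap is largely non-collapsibility: a marginal and a conditional odds ratio are different quantities.
- **SIBAR is the strongest prognostic score.** No passage says so. The correlation of 0.4 in 2.7 belongs to three other indicators (prior incapacity, unemployment and limited performance in the last occupation). The limitations section says that the screening instrument includes duration of incapacity, so SIBAR may overlap with a covariate already in the model.

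**Conclusion.** The point holds as a defect in specification. As written, section 2.9 does not define one model for the primary endpoint, and the same wording governs the dichotomous secondary outcomes. Its numerical weight is modest under the readings that converge: practically nil for a single random coefficient, and typically 2 to 6 % on the odds ratio for the site slope or the intercept per score value. For the intercept per value, the power loss is about 3 to 6 points if SIBAR is strongly prognostic. Only the patient-level slope is grossly unstable, and the article does not state that reading.

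A reader might infer that the primary comparison is biased or that its error rate is inflated. Neither has been shown, and randomisation still protects the comparison between groups.

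The sizes rest on an assumed SIBAR distribution and assumed effects, since the article gives neither. The finding itself does not: it follows from the text, with no grouping factor, one outcome per patient and site already fixed. I take the score meant to be the 0–19 social-medical index.

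**What to change.** In 2.9, remove the mention of random effects from the model description and replace the SIBAR sentence with:

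> *SIBAR measured before randomisation (the screening value used for the subgroup indication, or T0 only if completed before randomisation) enters as a continuous linear fixed-effect covariate.*

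Use the same model for the dichotomous secondary outcomes. With site already fixed, the primary model is then an ordinary logistic regression, as 2.7 assumes.

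The time point must be named. T0 is at the end of rehabilitation, surveys are completed within *marena*, and login details are sent only after randomisation, so the T0 score may be given when the patient already knows the allocation. SIBAR is one of the Table 1 criteria that clinic staff apply before randomisation, so an earlier value should exist. Confirm that it is recorded for both groups.

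The cost is an edit to 2.9, one line of model code and that check on the data. The sample size is unaffected.

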### Randomization

2.3

Participants will be randomized to either IG or CG in a 3:1 ratio, stratified by rehabilitation center. Randomization lists with permuted blocks of variable lengths will be created. Upon enrollment of participants by the clinic staff, the study team will access the respective randomization list provided by an independent researcher not otherwise involved in the study. If a participant is allocated to the CG, this is entered within *marena*. If a participant is allocated to the IG, the subgroup recommended by the clinical staff is entered within *marena.* Participants will be informed about their group assignment in the registration e-mail. Due to the nature of the interventions, blinding of the group assignment is not possible.

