### Outcome measures

2.6

Outcomes are assessed at the end of rehabilitation (T0) as well as three (T1), six (T2), nine (T3), and 12 months after discharge (T4). Table 2 provides an overview of the data collected at the five measuring points. We carefully selected compact instruments to reduce the burden on the participants.

**Table 2 t0010:** Schedule of assessments.

Construct	Questionnaire	T0	T1	T2	T3	T4
Primary Outcome						
Work status	employment status at 6 and 12 months of follow-up	x	x	x	x	x

Secondary Outcomes						
Successful completion of a graded return to work	Self-constructed items	x	x	x	x	x
Successful application for benefits for participation in working life	Self-constructed items	x	x	x	x	x
Current work ability	WAS^a^	x	x	x	x	x
Social-medical risk index	SIBAR^a^	x	x	x	x	x
Health related quality of life	EQ-5D^a^	x	x	x	x	x
Social Support	OSSS-3	x	x	x	x	x
Coping	BRCS	x	x	x	x	x
Anxiety	GAD-7	x	x	x	x	x
Depression	PHQ-9	x	x	x	x	x
Psychosocial Stress	PHQ-Stress	x	x	x	x	x
Somatic symptoms	SSS-8	x	x	x	x	x
Subjective prognosis of gainful employment	SPE	x	x	x	x	x
Satisfaction with *marena*	ZUF-8 *marena*^b^, ^d^			x		
Usability of *marena*	UEQ *marena*^b^, ^d^			x		
Helpfulness of *marena*	Self-constructed items^b^, ^d^			x		
Satisfaction with *GSA-Online plus*	ZUF-8 *GSA-Online plus*^c^, ^d^		x			
Usability of *GSA-Online plus*	UEQ *GSA-Online plus*^c^, ^d^		x			
Helpfulness of *GSA-Online plus*	Self-constructed items^c^, ^d^		x			

Other measures						
Demographics	Socio-Demographic Data	x				
Treatment data	Clinical Routine Data	x				
Occupational data	Clinical Routine Data	x				
Recommendations for rehabilitation aftercare	Clinical Routine Data	x				
General Feedback	Self-constructed items^b^		x	x		x
Adherence *marena*	Number of sessions in the intervention^b^, ^d^ Number of completed tasks^b^, ^d^ Number of completed weekly survey^b^, ^d^ Number of media playback^b^, ^d^ Number of visits to the intervention areas and individual pages^b^, ^d^	n. a.	n. a.	n. a.	n. a.	n. a.
Adherence *GSA-Online plus*	Number of completed writing-impulses^c^, ^d^	n. a.	n. a.	n. a.	n. a.	n. a.

a Work ability status, health condition and occupational stress are additionally provided in a weekly survey, so they are regularly answered during the intervention phase.

b Only participants of IG subgroup 1.

c Only participants of IG subgroup 2.

d Objective data collected within the programs.

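### Compound symmetry is the only covariance structure named for continuous outcomes at T0 to T4; if correlation falls with time between visits, baseline-referenced tests at 12 months exceed their nominal 5%

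*Protocol article*

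**What the plan says.** Section 2.9 (Statistical analysis for primary and secondary outcomes) of the protocol article states: "Continuous outcome measures will be analyzed with a covariance model for repeated measures". The next sentence fixes the structure: "Compound symmetry will be assumed". Section 2.9 gives no alternative structure, fit check or robust standard error. It does not say whether T0 enters as a response or as a covariate, or whether the test concerns one visit, a change from T0 or an average over visits.

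Section 2.6 (Outcome measures) sets the schedule: "Outcomes are assessed at the end of rehabilitation (T0) as well as three (T1), six (T2), nine (T3), and 12 months after discharge (T4". Ten scored scales appear at all five visits in Table 2: WAS, SIBAR, EQ-5D, OSSS-3, BRCS, GAD-7, PHQ-9, PHQ-Stress, SSS-8 and SPE.

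The primary analysis is separate. It is a logistic regression for the "dichotomous primary outcome work status at 6 months (T2, primary endpoint"). For the test level, section 2.9 says: "The significance level for all analyses will be defined as *p* = .05".

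**The concern.** Compound symmetry has two parameters. It requires the same variance at each visit, and the same correlation between visits 3 months apart as between visits 12 months apart. T0 falls at the end of inpatient care and T1 to T4 fall in everyday life. The two online programmes end at different times, GSA-Online plus after 12 weeks and marena after 6 months. The article gives no data to support a flat correlation across these phases, and for repeated symptom and work-ability scores a correlation that weakens with time is plausible.

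If it does weaken, the model applies one average residual variance to contrasts whose real variances differ. Early contrasts with baseline then look noisier than they are, and late ones look more precise. The tests and 95% confidence intervals for ten secondary outcomes depend on this.

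**Working it through.** **Inputs from the article.** Five visits, 3 months apart. Two-sided 5% (sections 2.7 and 2.9). Allocation 3:1 (section 2.3). Planned N = 400 with 20% dropout: 400 × (1 − 0.20) = 320, that is 240 IG and 80 CG. The article gives no figure for the continuous outcomes, so there is none to reproduce.

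**Assumed, because the article is silent.** Complete data, SD = 1 at every visit unless stated, and these correlation patterns:
- first-order autoregressive, AR(1), at 0.6 to 0.9 per 3 months
- linear decline from 0.70 (3 months apart) to 0.55 or to 0.40 (12 months apart)
- flat at 0.6

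**Method.** With complete data, compound symmetry estimates the average variance and the average covariance over visits. Let *ratio* be the compound-symmetry SE divided by the true SE. The real type I error is 2 × (1 − Φ(1.96 × ratio)). The ratio does not depend on the number of patients.

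**Change from T0, mild decline (0.70, 0.65, 0.60, 0.55).**
- Mean correlation over the 10 visit pairs: (4 × 0.70 + 3 × 0.65 + 2 × 0.60 + 1 × 0.55)/10 = 0.65.
- Group factor: √(1/240 + 1/80) = 0.129.
- Compound-symmetry SE: √(2 × 0.35) × 0.129 = 0.108 SD at every visit.
- True SE: √(2 × 0.30) × 0.129 = 0.100 SD at T1 and √(2 × 0.45) × 0.129 = 0.122 SD at T4.
- Ratios 1.08 and 0.88; real error 3.4% at T1 and 8.4% at T4.

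**Baseline-adjusted, AR(1) 0.8.**
- Residual variance given T0 is 1 − 0.8^(2k) at visit k: 0.36, 0.59, 0.74, 0.83; mean 0.63.
- Ratios √(mean/variance): 1.32, 1.03, 0.92, 0.87.
- Real error: 1.0%, 4.3%, 7.0%, 8.8% at T1 to T4.

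**All decay patterns, equal SDs (real error of the nominal 5% test).**

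| Pattern | Adjusted T1 / T2 / T4 | Change T1 / T2 / T4 |
|---|---|---|
| Linear 0.70 to 0.55 | 3.3 / 4.5 / 6.8% | 3.4 / 5.0 / 8.4% |
| Linear 0.70 to 0.40 | 2.3 / 4.3 / 7.7% | 2.4 / 5.0 / 11.0% |
| AR(1) 0.6 | 2.3 / 5.1 / 6.7% | 1.7 / 5.9 / 10.5% |
| AR(1) 0.7 | 1.6 / 4.8 / 7.6% | 1.3 / 5.7 / 11.9% |
| AR(1) 0.8 | 1.0 / 4.3 / 8.8% | 1.0 / 5.5 / 13.4% |
| AR(1) 0.9 | 0.5 / 3.6 / 10.4% | 0.8 / 5.3 / 15.0% |

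**Where the error vanishes or turns.**
- Flat correlation, equal SDs: ratio 1.00 for every contrast.
- Unadjusted level difference at a visit, equal SDs: ratio 1.00 under every pattern.
- Baseline-adjusted difference averaged over T1 to T4: ratio 1.00 under every pattern, because the average variance and covariance are exactly what this contrast needs. An averaged change from T0 is not protected; it runs at 6.7% to 10.2% under the patterns in the table.
- Flat correlation with SD falling from 1.2 to 1.0, baseline-adjusted: ratios 0.94 at T1 and 1.08 at T4, the opposite direction.
- Mild linear decline with the same falling SD, baseline-adjusted: 1.01 and 1.00, so the two departures nearly cancel.

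**The case against.** The article gives neither SDs nor correlations and does not say which contrast will be tested. A reader might infer that the planned standard errors are wrong as a matter of fact, too small at 12 months and too large at 3. The article does not support that: the working shows contrasts and patterns with no error, and one with the direction reversed. This part of the objection stands in full, and the point is conditional for that reason.

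The trial's main time point is T2, which is also when access to marena ends. Under the decay patterns tried, T2 contrasts run at 3.6-5.9%, close to nominal. Pure AR(1) decay is also a strong departure, since it leaves no stable between-person component: at 0.8 the T0-T4 correlation is 0.8^4 = 0.41. Under the mild linear decline the T4 error is only 6.8% (adjusted) or 8.4% (change). Both remarks limit the size of the problem but do not remove it.

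A reader might also infer that the trial's main conclusion is at risk. It is not, because the primary outcome is dichotomous and modelled by logistic regression. Nor can one infer that estimates will be biased under dropout. In principle a likelihood model with missing data leans on its covariance structure, and section 3.2 (Limitations) expects considerable dropout, but the article gives nothing from which to size such a bias.

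Finally, a full analysis plan may exist and may add robust standard errors, which would largely repair the SEs. Their absence from an article is no fault. The structure itself, however, is a choice the article states, not a detail it leaves open.

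**Conclusion.** The concern holds in conditional form. The article commits ten continuous secondary outcomes, measured over a year, to a two-parameter covariance structure and gives no support for it. If correlation falls with time between visits, SDs are about equal and model-based standard errors are used, baseline-referenced tests are conservative at T1 (SE about 8% to 44% too large) and anti-conservative at T4 (SE about 7% to 26% too small). The nominal 5% test at T4 then runs at about 7-10% (baseline-adjusted) or 8-15% (change from T0), with T2 close to nominal. These ranges rest on assumed correlations and complete data. The change is worth making because the restriction gains almost nothing if true and misstates precision if false. Its weight is moderate, since only secondary outcomes are involved.

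**What to change.** In section 2.9, or in the analysis plan if one governs, replace the compound-symmetry sentence with: *An unstructured covariance matrix will be used; if the model does not converge, a pre-specified simpler structure (e.g. heterogeneous Toeplitz) with robust standard errors will be used.*

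The cost is one sentence and one option in the code. With T0 as a response the matrix has 5 × 6/2 = 15 parameters; with T0 as a covariate, 4 × 5/2 = 10. With about 320 patients this loses almost no efficiency if compound symmetry is in fact true, and it brings the SE ratio to about 1 in every pattern tried. Section 2.9 places all analyses after the end of data collection, so the change can be fixed before any outcome is analysed.
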